## Abstract

**Background:**

CPAP is the gold standard treatment for obstructive sleep apnea (OSA) but suffers from poor long-term compliance. Alternatives like mandibular advancement devices (MADs) and surgery, such as transoral robotic surgery (TORS), are available, but their comparative efficacy is unclear.

**Study objective:**

This study aims to evaluate whether base of the tongue (BOT) reduction using TORS is equal or superior to CPAP and MADs in improving quality of sleep and life in patients with moderate to severe OSA eligible for surgery.

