In this proposed study, a trial designed to address a clinically pragmatic question: whether TORS, an accepted surgical treatment for selected patients but typically positioned after non-surgical therapies in the routine care pathway, provides outcomes that are equal or superior to standard non-surgical management. In this parallel-group, randomized controlled trial with a 1:1 allocation ratio, we will compare TORS to non-surgical therapy (CPAP or MADs). Following a superiority framework, it aims to determine whether TORS provides better sleep outcomes, long-term efficacy, and quality of life while assessing complications, compliance, and functional outcomes. These comparators were chosen because CPAP and MADs are well-established, non-invasive treatments recommended in clinical guidelines and are typically chosen as first options in routine care. Historically, surgery has been considered a last resort in the management of OSA. Therefore, CPAP and MAD are pooled as non-surgical therapy in this trial to reflect real-world conventional management rather than to compare TORS against a single treatment modality. The primary objective of this study is to quantify the effectiveness of TORS relative to CPAP or MADs in treating OSA. Additionally, this study aims to determine the long-term outcomes of TORS compared to conventional therapy, assess functional sleep outcomes in patients undergoing TORS. Furthermore, it will evaluate health-related quality of life in both treatment groups and examine patient compliance with non-surgical therapy. By addressing these objectives, this study aims to provide comprehensive insight into the role of TORS as a treatment modality for OSA, helping to inform clinical decision-making and improve patient outcomes.

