### Study outcomes

2.5

The primary endpoint of this study is the mean AHI measured 6 months post-intervention. This time point was selected because it reflects the earliest clinically relevant assessment at which treatment effects are expected to be stable in both arms: after postoperative recovery following TORS and after establishment of CPAP/MAD use and adherence. The PG will be performed at baseline, 6 months and 12 months. A lower AHI reflects improved airway patency and is thus clinically meaningful in assessing treatment effectiveness between groups. Twelve month follow up is included as an important secondary endpoint to evaluate durability of treatment effects in this chronic condition. Secondary outcomes include: (1) 50% reduction of AHI at 6 months compared to baseline and or AHI below 20/h (Sher's criteria) [2,21] reduction of AHI at 12 months to <5/h will be defined as surgical cure [3,22] differences in mean ODI 4% values at 6 months and 12 months, and reduction of ODI 4% to 25% relative to baseline will be defined as clinically relevant [4,22] differences between FOSQ-35 [15] scores at 3 months, 6 months and 12 months in which an increase of 10% of the score compared to baseline on the FOSQ-35 questionnaire will be defined as clinically relevant [5,22] differences between scores of ESS at 3 months, 6 months and 12 months and a reduction on the ESS to <10 will be defined as clinically relevant [6,23] differences between scores of quality of life questionnaires EQ-5D-5L [19] at 3 months, 6 months and 12 months [7]; differences in scores on the visual analogue scales (VAS) for snoring, tiredness and globus in all patients between baseline, 3, 6 and 12 months [8]; VAS scores swallowing and taste for patients in the TORS group at baseline compared to 3 months, 6 months and 12 months.

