### Sample size calculation

2.8

To answer our primary objective 25 patients per arm must be included in the study. This sample size calculation is based on results of an earlier RCT where OSA surgery was compared to conventional therapy (medical management) [26]. At 6 months MacKay et al. found the means of AHI to be in group 1, the conventional group 34.5 with a standard deviation of 23.0 and in group 2, the surgery group 20.8 with a standard deviation of 18.4. We have chosen to select a smaller standard deviation compared to the literature, as retrospective analysis of our database of OSA patients treated with TORS show a mean of AHI at 3 months (n = 31) of 16.4 with a standard deviation of 12.0 and a mean of AHI at 1 year (n = 14) of 10.8 with a standard deviation of 8.48. As our inclusion and exclusion criteria are strict and like our retrospective data and we expect a similar outcome. Given the sample size, analyses will primarily focus on estimating treatment effects with 95% confidence intervals. Secondary outcomes and subgroup analyses will be considered exploratory. Group sample sizes of 21 and 21 achieve 82% power to detect a difference of 10.0 between the null hypothesis that both group means are 34.0 and the alternative hypothesis that the mean of group 2 is 24.0 with estimated group standard deviations of 10.0 and 12.0 and with a significance level (alpha) of 0.05 using a two-sided two-sample *t*-test. The detectable differences are estimated to be of clinical relevance. To correct for possible missing data, we calculated a 20% bigger sample size which results in a sample size of 25 patients per arm.

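### The objective asks whether TORS is equal or superior, but the trial is sized and tested only for a difference, so equality cannot be concluded

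*Protocol article*

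**What the plan says.** All references are to the Protocol article.

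- **Abstract, Study objective:** the stated aim is as follows: "evaluate whether base of the tongue (BOT) reduction using TORS is equal or superior to CPAP and MADs in improving quality of sleep and life".
- **Introduction:** the pragmatic question is whether TORS "provides outcomes that are equal or superior to standard non-surgical management". The same paragraph then fixes the design: "Following a superiority framework, it aims to determine whether TORS provides better sleep outcomes".
- **Section 2.5, Study outcomes:** "The primary endpoint of this study is the mean AHI measured 6 months post-intervention".
- **Section 2.8, Sample size calculation:** "Group sample sizes of 21 and 21 achieve 82% power to detect a difference of 10.0". The hypotheses are "the null hypothesis that both group means are 34.0 and the alternative hypothesis that the mean of group 2 is 24.0". The SDs are 10.0 and 12.0, and the test is a two-sided two-sample t-test at alpha 0.05. The number is raised by 20% to 25 per arm. The section adds that the analyses will concentrate on treatment-effect estimates with 95% confidence intervals.
- **Section 2.10, Statistical analysis:** the primary outcome is compared by t-test or Mann-Whitney U, with significance at two-sided p<0.05.
- **Discussion:** the authors acknowledge the small sample and the type II error risk. They give estimates and intervals more weight than significance alone and promise caution with non-significant results.

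No margin, non-inferiority or equivalence hypothesis, or interval rule for concluding equality appears in the article.

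**The concern.** Asking whether one treatment is at least as good as another is a non-inferiority question, and asking whether two are equal is an equivalence question. Each needs a margin set in advance and a confidence interval compared with it. A test whose null hypothesis is equal means can reject equality but cannot establish it.

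The trial compares an operation with two established non-invasive treatments, and the Discussion says that the results should inform whether surgery moves earlier in the pathway. The Introduction lists surgical risks that the comparators do not carry. If the published objective still contains *equal* when the trial reports, a p-value above 0.05 could be presented as meeting it. At this sample size, such a result is compatible with TORS being materially worse or materially better on AHI.

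**Working it through.** **Inputs.** From section 2.8: SDs 10.0 and 12.0, difference 10.0, two-sided alpha 0.05, n = 21 evaluable and 25 randomised per arm. The margins are not in the document and are assumed here: 2.5, 5, 7.5 and 10 events/h.

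**1. Reproduce the stated power.**
Pooled SD = √((10² + 12²)/2) = √122 = 11.05.
SE at 21 per arm = √(244/21) = 3.41, so the noncentrality is 10/3.41 = 2.93 on 40 df.
Power = 81.7% (Welch 81.6%), against 82% stated. The figure reproduces, but it is the power to detect a difference.

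**2. Precision.** Half-width of the 95% interval = t(0.975, 2n−2) × √(244/n).
- n = 21: 2.021 × 3.41 = 6.89 events/h.
- n = 25: 2.011 × 3.12 = 6.28 events/h.

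So even an observed difference of exactly zero would leave differences of more than 6 events/h in either direction inside the interval.

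These widths depend on the planned SDs. Section 2.8 also quotes a control-arm SD of 23.0 from the earlier RCT. With 23.0 in one arm and 12.0 in the other, the half-width is 2.011 × √(673/25) = 10.4 at 25 per arm and 2.021 × √(673/21) = 11.4 at 21. It reaches 13.0 at 21 per arm only if the other arm also takes that RCT's surgical SD of 18.4: 2.021 × √(867.56/21).

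**3. How often a real difference gives p>0.05** (noncentral t, planned SDs, either direction):

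| True difference (events/h) | n = 21 | n = 25 |
|---|---|---|
| 2.5 | 89% | 88% |
| 5 | 70% | 65% |
| 7.5 | 43% | 35% |
| 10 | 18% | 12% |

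**4. What a non-inferiority claim would need.** True difference 0, one-sided alpha 0.025. Power is from the noncentral t with noncentrality margin/SE. Required n per arm at 80% power is 2 × (11.05 × (1.960 + 0.842)/margin)², before dropout.

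| Assumed margin (events/h) | Power, n = 21 | Power, n = 25 | n per arm for 80% |
|---|---|---|---|
| 2.5 | 11% | 12% | 307 |
| 5 | 30% | 35% | 77 |
| 7.5 | 57% | 65% | 35 |
| 10 | 82% | 88% | 20 |

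Of these margins, only 10 events/h reaches 80% power at the planned size, and that margin equals the whole difference the trial is designed to detect. Two-sided equivalence, with the 95% interval inside ± the margin, needs slightly more: 411, 103, 46 and 26 per arm.

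**The case against.** Every operative part of the plan is consistent with superiority: the declared framework, the null hypothesis, the sample size and the test. Nowhere does the article say that p>0.05 will be taken as equality. Sections 2.8 and 3 say the opposite in spirit, by favouring estimates and intervals, naming the type II error risk and promising caution. On this view, the objective is loosely worded and the design statement in the same Introduction paragraph settles it.

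Much of this stands. It shows that the problem is one of wording and that the sponsor has already taken steps against the misreading. It does not supply what is missing, because an interval can support *equal* only against a margin, and a promise of caution does not say that non-significance is not equality.

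Three stronger readings are not supported:

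- A reader might infer that the sponsor plans to claim equality from a non-significant test. No such rule is stated.
- A reader might infer that the sample size is miscalculated. The stated power reproduces for the test it describes.
- A reader might infer that superiority of TORS is the only conclusion open to the trial. The test is two-sided, so it can also show that TORS is worse.

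**Conclusion.** The concern holds as a conflict between the stated objective and the design, and it should be fixed. It does not invalidate the design. The *equal* half of the objective has no hypothesis, margin or decision rule, and the sample is too small to support it at any assumed margin clearly below the planned effect: power is 30 to 35% at 5 events/h and 57 to 65% at 7.5.

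The textual conflict needs no assumption. The figures for precision and non-significance rest on the planned SDs of 10.0 and 12.0; larger SDs would widen the intervals. The non-inferiority figures also rest on assumed margins and a true difference of zero, which is why a range is shown.

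**What to change.** 1. Delete *equal or* from the abstract's Study objective and from the Introduction.
2. State the primary question as a difference in mean AHI at 6 months between TORS and non-surgical therapy, in line with section 2.5. The abstract's objective currently refers to quality of sleep and life.
3. Add to section 2.10: *The primary test can show a difference in either direction; a non-significant result will be reported as inconclusive with its 95% CI and not as equality or non-inferiority.*

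This changes wording only; the sample size, endpoint and test stay as they are. The sponsor gives up an equality claim that the design could not support.

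If that claim is wanted, the alternative is a justified margin, an interval rule and a new sample size. At an assumed margin of 5 events/h, non-inferiority would need about 77 evaluable patients per arm, or 77/0.8 = 97 randomised per arm if 20% are lost.

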**Study design:**

A prospective randomized controlled trial.

**Population:**

Patients eligible for TORS and CPAP or MAD aged >18 years with moderate to severe OSA (Apnea Hypopnea Index >15) untreated before.

**Interventions:**

In total 50 patients, 25 in each treatment arm will be randomized to either TORS or non-surgical therapy (CPAP or MAD depending on preference of patient or physician).

**Outcome measures:**

Primary outcomes will include improvement in sleep apnea severity measured through the apnea hypopnea index (AHI) and oxygen desaturation index (ODI)4%. Secondary outcomes will assess long-term quality of life compared to non-surgical therapy and adherence to devices.

**Results:**

The data will be analysed on an Intention-To-Treat principle (ITT). Ethical approval was obtained from RTPO in September of 2023. Trial registration number: NL84446.099.23 METCnumber UMCG25.327. Outcomes will be published in peer reviewed journals and presented at (inter)national conferences.

**Discussion:**

Findings of this study will address the evidence gap in the comparative effectiveness of TORS versus non-surgical therapies for OSA and may inform future clinical decision making and guideline development.

## Introduction

1

In obstructive sleep apnea (OSA) syndrome, repetitive partial or complete collapse of the upper airway during sleep leads to nocturnal hypoxia and interruption leading to daytime sleepiness [1]. OSA is associated with an increased risk of comorbidities such as hypertension, type 2 diabetes mellitus, and cardiovascular disease [2,3]. The gold standard treatment for OSA is continuous positive airway pressure (CPAP). CPAP effectively reduces apnea hypopnea index (AHI), improves sleep quality and decreases cardiovascular co-morbidities [4,5]. Regardless of the benefits, 30% of patients refuse treatment with CPAP due to several reasons including pressure effect of the mask [4] [[5], [6], [7]]. Another challenge of CPAP is treatment adherence, which requires a minimum usage of 4 h per night on at least 70% of nights. A study by Koehler et al. has shown that after 3 months adherence rates were 54% [8]. Mandibular advancement devices (MADs) are another non-surgical treatment modality that effectively reduce AHI [9], though they are less effective than CPAP. However, MADs demonstrate higher treatment adherence compared to CPAP [10].

For OSA patients who are unable to tolerate CPAP or MADs and are eligible for surgery, transoral robotic surgery (TORS) has emerged as an effective treatment option. TORS focuses on the obstruction at BOT, permanently enlarging the upper airway by removing lingual tonsil tissue. However, like all surgeries, TORS carries inherent risks such as postoperative bleeding, stenosis, infection and dysphagia, all risks that non-surgical therapies do not present. While studies have shown that TORS effectively reduces AHI [11,12], randomized trials comparing its efficacy to standard non-surgical therapies are lacking.

In this proposed study, a trial designed to address a clinically pragmatic question: whether TORS, an accepted surgical treatment for selected patients but typically positioned after non-surgical therapies in the routine care pathway, provides outcomes that are equal or superior to standard non-surgical management. In this parallel-group, randomized controlled trial with a 1:1 allocation ratio, we will compare TORS to non-surgical therapy (CPAP or MADs). Following a superiority framework, it aims to determine whether TORS provides better sleep outcomes, long-term efficacy, and quality of life while assessing complications, compliance, and functional outcomes. These comparators were chosen because CPAP and MADs are well-established, non-invasive treatments recommended in clinical guidelines and are typically chosen as first options in routine care. Historically, surgery has been considered a last resort in the management of OSA. Therefore, CPAP and MAD are pooled as non-surgical therapy in this trial to reflect real-world conventional management rather than to compare TORS against a single treatment modality. The primary objective of this study is to quantify the effectiveness of TORS relative to CPAP or MADs in treating OSA. Additionally, this study aims to determine the long-term outcomes of TORS compared to conventional therapy, assess functional sleep outcomes in patients undergoing TORS. Furthermore, it will evaluate health-related quality of life in both treatment groups and examine patient compliance with non-surgical therapy. By addressing these objectives, this study aims to provide comprehensive insight into the role of TORS as a treatment modality for OSA, helping to inform clinical decision-making and improve patient outcomes.

## Methods

2

### Study setting

2.1

This study is single-site, two-arm, parallel-group, randomized controlled trial, in a general hospital, the Frisius Medical Center located in Leeuwarden, the Netherlands. The trial aims to compare the clinical effectiveness of TORS versus non-surgical therapy (CPAP or MAD) in patients with moderate to severe OSA and will include 50 patients eligible for surgery randomized into either group 1 receiving TORS BOT reduction (*n* = 25) or group 2 CPAP or MAD (*n* = 25), depending on clinical preference. The duration of the trial is estimated to be approximately two years. The trial design is visualized in Fig. 1.

**Fig. 1 fig1:**
[figure not shown]
Overview of the design of the RAPID randomized controlled trial.

### Eligibility criteria

2.2

All patients presented at the otorhinolaryngology department of the Frisius Medical Center with a diagnosis of moderate to severe OSA eligible for surgery based on physical examination, respiratory polygraphy (PG) and drug induced sleep endoscopy (DISE) will be screened for eligibility. Inclusion criteria include [1]: age of at least 18 years or older [2]; ability to understand and comply with the protocol requirements, and provide written informed consent [3]; AHI of equal to or more than 15 on PG [4]; physical examination showing lingual tonsils classified as Friedman grade 3 or 4; and [5] DISE demonstrating collapse at BOT level classified as grade 2. Exclusion criteria include [1]: body mass index higher than 32 [2]; concentric collapse during DISE [3]; symptoms of Central Sleep Apnea Syndrome [4]; high co-morbidity as determined by American Society of Anaesthesiologists (ASA) score of 4 (severe systemic disease that is a constant threat to life) [5]; history of psychiatric hospitalization [6]; excessive use of opiates or benzodiazepines; and [7] previous treatment of CPAP and/or MAD or inability to tolerate MAD.

### Study interventions

2.3

Participants randomized to the surgical arm will undergo TORS with BOT reduction, a technique established by Vicini et al. in 2010 [13]. In the Netherlands it is an accepted and well tolerated technique to reduce the BOT [14]. Procedures will be performed under general anaesthesia by two head and neck surgeons of the Frisius Medisch Centrum Leeuwarden, following standardized protocols. Postoperative care includes a short clinical stay of 3 days and a clinical follow-up visit at 6 weeks.

Participants randomized to the control arm will receive non-surgical therapy, consisting of the gold standard treatment, CPAP or MAD, as determined by shared decision-making between patient and their physician. CPAP devices (Airsense 10 AutoSet, Airsense 10 Elite, Airsense 11 Autoset or Airsense 11 Elite) will be prescribed by the pulmonologists of the Frisius Medisch Centrum Leeuwarden and will be tailored to patient needs. CPAP devices will be fabricated by ResMed. Adherence data will be remotely monitored.

Participants receiving MAD will be evaluated by a maxillofacial oral surgeon and fitted with custom adjustable devices manufactured by SomnoMed, SomnoDent Flex. The MAD will be made in the dental laboratory of the Frisius Medisch Centrum Leeuwarden.

CPAP and MAD users will receive standardized counseling regarding usage, side effects, and expectations. Technical or adherence issues will be addressed through telephone follow-up and in-person visits as needed.

The following interventions are prohibited during the trial period [1]: use of CPAP or MAD after intervention via TORS [2]; other concomitant transoral surgery such as (bi maxillary) osteotomy [3]; other concomitant OSA treatment such as position therapy, hypoglossal nerve stimulation, nasal resistors, oropharyngeal exercises.

### Questionnaires

2.4

The Functional Outcomes of Sleep Questionnaire (FOSQ-35) evaluates the impact of sleep disorders on daily functioning, with higher scores reflecting better functional status [15] and is validated in Dutch. An increase of ≥2 points from baseline is considered clinically meaningful [16]. Daytime sleepiness will be assessed using the validated Epworth Sleepiness Scale (ESS) [15], which comprises eight items scored from 0 to 3, yielding a total score between 0 and 24. A score below 10 is generally considered normal among healthy adults [17]. Swallowing-related quality of life will be measured using the MDADI [18], which ranges from 20 to 100; scores between 80 and 100 suggest normal swallowing ability. The EuroQol 5-Dimension 5-Level questionnaire (EQ-5D-5L) is a standardized tool to assess health-related quality of life across five domains: mobility, self-care, usual activities, pain/discomfort, and anxiety/depression. Each domain has five severity levels, plus a visual analogue scale from 0 to 100 to rate overall health [19]. The Swallowing Quality-of-Life Questionnaire (SWAL-QoL) is a validated tool assessing how swallowing problems affect daily life. It covers physical, emotional, and social aspects, with higher scores indicating better quality of life [20].

### Study outcomes

2.5

The primary endpoint of this study is the mean AHI measured 6 months post-intervention. This time point was selected because it reflects the earliest clinically relevant assessment at which treatment effects are expected to be stable in both arms: after postoperative recovery following TORS and after establishment of CPAP/MAD use and adherence. The PG will be performed at baseline, 6 months and 12 months. A lower AHI reflects improved airway patency and is thus clinically meaningful in assessing treatment effectiveness between groups. Twelve month follow up is included as an important secondary endpoint to evaluate durability of treatment effects in this chronic condition. Secondary outcomes include: (1) 50% reduction of AHI at 6 months compared to baseline and or AHI below 20/h (Sher's criteria) [2,21] reduction of AHI at 12 months to <5/h will be defined as surgical cure [3,22] differences in mean ODI 4% values at 6 months and 12 months, and reduction of ODI 4% to 25% relative to baseline will be defined as clinically relevant [4,22] differences between FOSQ-35 [15] scores at 3 months, 6 months and 12 months in which an increase of 10% of the score compared to baseline on the FOSQ-35 questionnaire will be defined as clinically relevant [5,22] differences between scores of ESS at 3 months, 6 months and 12 months and a reduction on the ESS to <10 will be defined as clinically relevant [6,23] differences between scores of quality of life questionnaires EQ-5D-5L [19] at 3 months, 6 months and 12 months [7]; differences in scores on the visual analogue scales (VAS) for snoring, tiredness and globus in all patients between baseline, 3, 6 and 12 months [8]; VAS scores swallowing and taste for patients in the TORS group at baseline compared to 3 months, 6 months and 12 months.

Other study parameters will be descriptive parameters such as age, gender, body mass index, history of smoking, reflux complaints, dentition, history of medication use including sleep medication, physical examination (Friedman score of the tongue tonsils and throat tonsils), measurements of DISE such as tongue base collapse classified by velum oropharynx tongue base epiglottis classification system (VOTE) [24]. Other PSG measurements are also included as study parameters such as ODI 4%, lowest desaturation (LSAT), desaturations below 90%, number of hypopneas, number of apneas and snoring time. For CPAP and MAD compliance will be assessed by pulmonologists and maxilla oral facial surgeons including follow up time, start date of treatment. Quality of life assessments and swallowing quality through MDADI [18] and SWAL-QoL [20] at baseline 3 months, 6 months and 12 months for the TORS group.

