### Statistical analysis

2.10

All statistical analyses will be conducted using IBM SPSS Statistics. The full analysis set (FAS) follows the Intention-To-Treat (ITT) principle and includes all planned subjects, except those with major protocol violations, no post-baseline data, or no study intervention.

Baseline characteristics, including age, gender, BMI, PG, ENT exam, DISE results, smoking, and reflux history, will be summarized using descriptive statistics. Quantitative variables will be presented as mean and standard deviation or as median with interquartile range or minimum/maximum, and qualitative data as frequencies and percentages, with 95% confidence intervals where applicable. Data normality will be assessed graphically and numerically. No formal statistical tests will be performed for baseline comparisons. The primary outcome (AHI at 6 months) will be analysed using independent *t*-test or Mann-Whitney *U* test depending on data distribution. Given the RCT design, adjustments for baseline differences are not foreseen. In case of missing data this will be mentioned in the results. Missing data will not be replaced. For all hypothesis testing, a two-sided p-value of less than 0.05 indicates statistical significance. Secondary outcomes will follow the same approach. For continuous variables, appropriate group comparisons (*t*-test, Mann–Whitney U, ANOVA, or Kruskal–Wallis) will be used. For categorical outcomes, Fisher's exact or Chi-square tests will be applied as applicable. Because the control arm includes two standard non-surgical modalities (CPAP and MAD), additional prespecified analyses will be performed to assess robustness. These include [1] subgroup analyses comparing TORS vs CPAP and TORS vs MAD separately (exploratory due to sample size) and [2] sensitivity analyses adjusting for control modality (CPAP vs MAD) when evaluating the primary endpoint. Treatment adherence data will be reported descriptively and considered when interpreting outcomes. Other study parameters will be analysed descriptively as outlined above.

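### The 6-month AHI response rule joins its two limbs with 'and or', so one permitted reading counts patients who have not improved; the FOSQ-35 threshold is also stated in two ways

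*Protocol article*

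**What the plan says.** Protocol article, section 2.5 (Study outcomes), lists as its first secondary outcome "50% reduction of AHI at 6 months compared to baseline and or AHI below 20/h", and labels this with the name of a published criterion. Section 2.2 (Eligibility criteria) sets entry at "AHI of equal to or more than 15 on PG"; the abstract puts it as strictly above 15. Neither place has a floor at 20/h.

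For the FOSQ-35, section 2.4 (Questionnaires) states: "An increase of ≥2 points from baseline is considered clinically meaningful". Section 2.5 states that "an increase of 10% of the score compared to baseline on the FOSQ-35 questionnaire will be defined as clinically relevant".

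Section 2.10 (Statistical analysis) plans between-arm tests of responder-type outcomes: "For categorical outcomes, Fisher's exact or Chi-square tests will be applied as applicable". Section 2.8 declares secondary outcomes exploratory. The primary endpoint is mean AHI at 6 months and uses neither rule.

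**The concern.** A response rule should separate patients who improved from those who did not. The second limb of the AHI rule is an absolute level that lies above the entry threshold. If that limb is enough by itself, anyone enrolled at 15 to just under 20/h meets it already and keeps meeting it at 6 months without improving. The *or* reading also admits patients who start at 20/h or more and drift below 20 without halving their AHI, and patients who halve it without reaching 20.

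The reported response rate therefore depends on a connective that the plan leaves open. The trial is open-label, and responder rates are easily quoted, so the choice should not be left until results are visible. The FOSQ-35 raises a smaller question of the same kind: two statements of what change matters on one instrument.

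**Working it through.** **The plan's own figures.** The plan gives no expected responder rate to reproduce. Its one power figure (82%; 21 per arm, difference 10, SDs 10 and 12) concerns the primary endpoint. SE = √(100/21 + 144/21) = 3.41, and the noncentral t with 40 df gives 81.7%, so it reproduces. It does not involve the response rule.

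**Step 1: apply the rule to single patients.** Let *halved* mean that the 6-month AHI is at most 0.5 × baseline, and *low* that the 6-month AHI is below 20.

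| Baseline → 6 months | Halved | Low | *or* | *and* |
|---|---|---|---|---|
| 18 → 18 | no | yes | responder | not |
| 18 → 19.5 | no | yes | responder | not |
| 30 → 19 | no | yes | responder | not |
| 60 → 29 | yes | no | responder | not |
| 16 → 7.9 | yes | yes | responder | responder |

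The first two rows need only the entry threshold and the rule as written, with no assumption about distributions.

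**Step 2: how many could start below 20/h.** The baseline AHI distribution is not given, so this is an assumption. Take baseline = 15 + G, with G gamma, mean 19 (overall mean 34) and SD s. Shape is (19/s)², scale is s²/19, and the share below 20 is P(G < 5).

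- s = 10: 3%
- s = 12: 7%
- s = 15: 14%
- s = 23: 32%

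The mean of 34 and the SDs of 10, 12 and 23 are borrowed from section 2.8, where they describe AHI at follow-up and not at baseline; 15 is an intermediate value. As a check on shape, normal and lognormal distributions truncated at 15, with means of 25 to 34.5 and SDs of 10 to 23, give 4–25%, or about 2–13 of 50 patients.

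**Step 3: responder rate with no treatment effect.** Take s = 15 and 6-month AHI = baseline × exp(σZ), with Z standard normal and an assumed σ of 0.3 to 0.4. The chance of halving is Φ(ln 0.5/σ), which is 1% at σ = 0.3 and 4% at σ = 0.4, so the *and* rate cannot exceed that. By simulation:

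- *or*: 19–23%, or about 5–6 of 25 patients in an arm (0.19 × 25 = 4.75; 0.23 × 25 = 5.75)
- *and*: 1–3%, fewer than 1 of 25

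Of the 19–23%, about 8–9 points come from patients who start below 20, and about 10–14 points from patients who start at 20 or more and mostly drift under it.

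**Step 4: does the between-arm difference shrink under *or*?** Use the same model with σ = 0.5 and median ratios of 0.7 in one arm and 0.5 in the other.

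- *or*: 48% against 70%, a difference of 22 points
- *and*: 22% against 45%, a difference of 23 points

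The levels differ greatly; the differences are almost the same.

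**Step 5: FOSQ-35.** The two thresholds agree where 0.10 × B = 2, which is B = 20. At illustrative baselines of 10, 14 and 18, the 10% rule needs 1.0, 1.4 and 1.8 points against 2 points. The article does not give the scale range, so these baselines are examples only.

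**The case against.** The strongest reply is that *and* may be what is meant. The rule carries the name of a published criterion, and that source may settle the connective. This stands as far as it goes: a reader might infer that the plan definitely counts patients enrolled at 15–20/h as responders, and the text does not support that. It supports only that the wording permits it. The source is not at hand, and the article's own words do not resolve the point.

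A reader might also infer that the *or* reading dilutes the contrast between arms. Step 4 does not bear this out: the risk difference is 22 points under one reading and 23 under the other.

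A third tempting extension is to the ESS, where "a reduction on the ESS to <10 will be defined as clinically relevant" and there is no ESS entry criterion. That is not the same flaw, because the wording demands a reduction: a patient who stays at 9 does not qualify.

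On the FOSQ-35, section 2.4 reads as background on the instrument and section 2.5 as the trial's own definition. The 10% rule is therefore the natural operative one, and it would overstate the case to call the choice wholly open. Still, both sentences say what change is clinically important and nothing ranks them.

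Finally, the baseline inputs are follow-up planning values. That is correct, and it is why Step 2 is given as a range whose upper end depends on an SD of 23. More than half of the no-effect responders under *or* start at 20 or above, so the rates in Step 3 are not a measure of the low-baseline problem alone.

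**Conclusion.** The point holds as an ambiguity with a real consequence. One permitted reading of the AHI rule classes patients with a baseline of 15 to below 20/h as responders when they are unchanged or slightly worse, and also counts drift below 20 without halving; the other reading does neither. That follows from the text alone.

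The size rests on assumptions: about 3–32% of patients starting below 20/h (3–7% at SD 10–12), and a no-effect responder rate of about 19–23% against 1–3% at SD 15. A narrower baseline spread lowers the *or* figure. The FOSQ-35 mismatch is a smaller matter of consistency. Because the outcomes affected are secondary and exploratory, the main comparison is not threatened; what needs protecting is the meaning of the reported response rates.

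**What to change.** In section 2.5, define AHI response as a reduction of at least 50% from baseline AND an AHI below 20/h at 6 months. This removes the possibility of responding without improving. The downside is that stated responder rates will be lower.

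Make sections 2.4 and 2.5 agree on one prespecified FOSQ-35 threshold. If the 10% rule is the operative one, say so, and mark the 2-point figure in section 2.4 as background only. The arithmetic gives no reason to prefer either.

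Both are wording edits that need no extra patients, visits or data. They should be made before outcome data are examined.
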